#### Knowledge

##### Questionnaire

At the end of the project, a questionnaire will be distributed to the health professionals involved in the experimental and control groups by their organization of employment. This will help ensure the privacy of contact information. The questionnaire is composed of two questions regarding the assessment of the health professional. It assesses his or her knowledge on the frail elderly and his or her knowledge of the roles and tasks of other health professionals involved in the care for the frail elderly. Answers are given for the current situation and the situation 18 months previously and are measured with a VAS ranging from 0 to 10.

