**Methods/design:**

The design is quasi-experimental. Effects will be measured by conducting a before and after study with control group. The experimental group will consist of 220 elderly of 8 GPs (General Practitioners) who will provide care according to the integrated model (The Walcheren Integrated Care Model). The control group will consist of 220 elderly of 6 GPs who will give care as usual. The study will include an evaluation of process and outcome measures for the frail elderly, their caregivers and health professionals as well as a cost-effectiveness analysis. A concurrent mixed methods design will be used. The study population will consist of elderly 75 years or older who live independently and score a 4 or higher on the Groningen Frailty Indicator, their caregivers and health professionals. Data will be collected prospectively at three points in time: T0, T1 (3 months after inclusion), and T2 (12 months after inclusion). Similarities between the two groups and changes over time will be assessed with t-tests and chi-square tests. For each measure regression analyses will be performed with the T2-score as the dependent variable and the T0-score, the research group and demographic variables as independent variables.

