**Use of community services**				
Self-reported	Interview caregiver or mailed questionnaire	x	x	x
CSAI	Interview caregiver or mailed questionnaire	x		x

**Table 3 T3:** Outcome measures and data collection health professionals

**Outcome and instrument**	**Method**	**Data collection time**		
		**T0**	**T1**	**T2**

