**Knowledge**				
Self-constructed VAS	Mailed questionnaire	x		x

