**Job satisfaction**				
Job satisfaction scale	Mailed questionnaire	x		x

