**Subjective burden**				
SRB	Mailed questionnaire	x		x

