#### Degree of integration

##### Questionnaire

To determine the degree of coherence, continuity, and co-operation, a questionnaire will be developed based on a systematic review of integration indicators and instruments for measuring integration. The questions will be part of the questionnaire sent to the health professionals as described above. Health professionals are again asked to assess the current levels of integration and those 18 months previously.

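### Four health-professional measures are scheduled as a T0 baseline, but the text collects that baseline by recall at project end and then analyses it as a T0-score

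*Protocol article*

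**What the plan says.** The abstract states: "Data will be collected prospectively at three points in time: T0, T1 (3 months after inclusion), and T2 (12 months after inclusion"). Table 3 ("Outcome measures and data collection health professionals") has columns for data collection time. It ticks T0 and T2, by mailed questionnaire, for knowledge ("Self-constructed VAS"), job satisfaction ("Job satisfaction scale") and subjective burden. Table 4 ticks T0 and T2 for degree of integration.

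The instrument text gives another schedule. Under Knowledge: "At the end of the project, a questionnaire will be distributed to the health professionals involved in the experimental and control groups". On timing it adds: "Answers are given for the current situation and the situation 18 months previously". Job satisfaction belongs to the same questionnaire and is also rated for now and for 18 months earlier. The subjective-burden scale uses the same two reference points. Under Degree of integration: "Health professionals are again asked to assess the current levels of integration and those 18 months previously". No baseline mailing to professionals is described.

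The Data analysis section plans t-tests of change over time for every process and outcome measure. For every measure it also plans a regression of the T2-score on the T0-score, research group and demographic variables. Recalled scores get no separate treatment.

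**The concern.** The two schedules cannot both be followed. A reader of the tables or the abstract would believe that professionals gave a baseline before the model was introduced. The text describes none.

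The difference carries into the analysis. A baseline covariate should not be open to influence by the intervention. Here the supposed T0-score is given after exposure, in the same questionnaire as the current score, by staff who know which group they worked in; the Evaluation study section says blinding is not possible. Training in the model could change how staff rate their own earlier knowledge or the earlier level of integration. Because groups are not randomised, the T0-score is also a main tool for handling initial differences between them.

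At stake are quantitative results on health professionals and on the organization of care, both named in the research question.

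**Working it through.** **Step 1. The schedules side by side.**

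| Measure | Table schedule | Instrument text |
|---|---|---|
| Knowledge | Table 3: T0, T2 | One questionnaire at project end; current and 18 months earlier |
| Job satisfaction | Table 3: T0, T2 | Part of that questionnaire; current and 18 months earlier |
| Subjective burden | Table 3: T0, T2 | Current and 18 months earlier |
| Degree of integration | Table 4: T0, T2 | Part of the same questionnaire; current and 18 months earlier |
| Objective burden | Table 3: T0, T1, T2 | Elder interviews, GP files, time tracking; no 18-month recall |

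The contradiction covers the first four rows only.

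**Step 2. What a recalled baseline does to the planned analyses.** The protocol gives no figure to reproduce. The inputs below are assumptions, not document values, with the outcome SD set to 1:

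- r: within-group correlation of true T0 and T2, 0.5 to 0.7
- λ: pull of recall toward the present state, 0 to 0.6
- s: extra recall shift in the experimental group, 0 or −0.3 (past remembered as worse)
- e: true effect, 0 or 0.3

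Recalled score: R = (1−λ)·T0 + λ·T2 + s·group. The groups then differ in R by λe + s.

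- Difference in change = e − (λe + s) = (1−λ)e − s
- Adjusted group effect = e − b(λe + s), where b = [(1−λ)r + λ] / [(1−λ)² + λ² + 2λ(1−λ)r]

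Worked example, r = 0.5 and λ = 0.3: b = (0.35 + 0.30)/(0.49 + 0.09 + 0.21) = 0.65/0.79 = 0.823. With e = 0 and s = −0.3, the adjusted effect is 0.823 × 0.3 = 0.247. With e = 0.3 and s = 0, it is 0.3 − 0.823 × 0.09 = 0.226.

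| r | λ | b | Adjusted effect, e = 0, s = −0.3 | Adjusted effect, e = 0.3, s = 0 |
|---|---|---|---|---|
| 0.5 | 0 | 0.500 | 0.150 | 0.300 |
| 0.5 | 0.3 | 0.823 | 0.247 | 0.226 |
| 0.5 | 0.6 | 1.053 | 0.316 | 0.111 |
| 0.7 | 0 | 0.700 | 0.210 | 0.300 |
| 0.7 | 0.3 | 0.904 | 0.271 | 0.219 |
| 0.7 | 0.6 | 1.028 | 0.308 | 0.115 |

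The difference in change is 0.30 throughout the fifth column's scenario. In the last column's scenario it is 0.7 × 0.3 = 0.21 at λ = 0.3 and 0.4 × 0.3 = 0.12 at λ = 0.6. With e = 0 and s = 0, both analyses give zero. A simulation of 400,000 respondents under the same model agrees with these values to within 0.005.

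**Step 3. Numbers of respondents.** The sampling section expects about 400 questionnaires sent and a 50% response: 400 × 0.5 = 200 returns. With two mailings, complete pairs would be 400 × 0.5 × 0.5 = 100 if responses in the two waves were independent, and 200 if the same people answered both. Independence is an assumption.

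**The case against.** The strongest reply is that then-and-now rating is a deliberate and disclosed design, described in the same way for all four measures. It has a merit: after training, professionals may judge their knowledge by a different standard, and rating both points in one sitting holds that standard constant. This stands as an argument for the format. It does not explain why the tables and abstract show a prospective baseline, or why the analysis treats the recalled score like any measured T0-score.

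Several stronger readings are tempting and are not supported:

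- *That the observed changes are recall artefacts.* The documents show values open to bias, not that bias occurs. With no true effect and equal recall error in both groups, the bias is zero.
- *That all professional outcomes are affected.* Objective burden is not. Table 4 also ticks T0 and T2 for the satisfaction questionnaire and the relational coordination survey, but the text does not say that these are recalled. Professionals' experience and the organization of care are also studied through diaries, interviews, focus groups and reports from elderly and caregivers.
- *That 18 months is wrong because T0 to T2 is 12 months.* The 12 months run from the inclusion of elderly and caregivers. No inclusion date for professionals, recruitment period or project length is given, so no error can be shown. The look-back is simply not tied to a named date.
- *That bias must favour the model.* It can equally hide a benefit.
- *That the recalled score should be dropped and only T2 compared.* With 3 practices in the east against 5 elsewhere in the region, that would leave existing differences uncontrolled.

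**Conclusion.** The concern holds for four measures: knowledge, job satisfaction, subjective burden and degree of integration. Their schedule is contradictory, and if the text is followed, a recalled value given after exposure enters the regression and the change tests as though it were a measured baseline.

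The actual size of any bias is unknown. Under the assumptions shown, a 0.3 SD group difference in recall creates a false adjusted effect of 0.15 to 0.32 SD and a false difference in change of 0.30 SD. A 30% to 60% pull toward the present reduces a true 0.3 SD effect to between 0.23 and 0.11 SD (adjusted), or between 0.21 and 0.12 SD (change). These figures illustrate direction and scale; they do not predict the trial's results.

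The elderly's quality of life, its power calculation and the EQ-6D input to the economic analysis are untouched. The point should be corrected because it changes what these secondary results can support, but it does not threaten the main comparison.

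**What to change.** **If T0 has not passed:** send the questionnaire at T0, as Tables 3 and 4 already show, and use that answer as the T0-score. Distribute it through the employers, as planned for project end, with an anonymous code to link the two returns. Replace the recall wording in the four instrument descriptions. The cost is one extra mailing of about 400 questionnaires, a linking scheme, and fewer complete pairs (roughly 100 to 200, as worked above).

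**If T0 has passed:**

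1. Relabel the T0 ticks for these four measures in Tables 3 and 4 as *recalled at T2*, and limit the abstract's claim of prospective collection to the other data.
2. Anchor the recall period to the start of the intervention.
3. Give these measures their own analysis wording: compare current scores between groups with and without the recalled score, and report both as retrospective evidence.
4. Treat recalled change as supportive only.
5. State both limitations: recall bias, and residual confounding from non-random groups without a measured baseline.

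This second route costs only changes to tables and text, plus one extra model per measure. The price is a weaker claim about change.

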#### Job satisfaction

##### Job satisfaction scale

The job satisfaction scale will be part of the questionnaire. This instrument is a 10-item questionnaire with questions on extrinsic and intrinsic job satisfaction [58,59]. Health professionals will be asked to assess how satisfied they are now and 18 months previously on a scale ranging from 1 (‘extremely unsatisfied’) to 7 (‘extremely satisfied’).

#### Subjective burden

##### Self-related burden VAS

Inspired by the SRB, a similar VAS will be used to measure the overall perceived burden. As the SRB was developed for caregivers, the question will be transformed into the question ‘How straining is it to give care to the frail elderly?’ Scoring measures the current situation and the situation 18 months previously with a horizontal VAS ranging from 0 (‘not straining at all’) to 10 (‘much too straining’).

#### Objective burden

##### File research and questionnaire

File research and the questions on healthcare use by the elder as mentioned above will be used to determine the time spent on care. For the time calculation, the volume of care will be multiplied by a mean time determined by consensus with the health professionals (e.g., 40 minutes per house visit by a GP).

##### Time tracking form

The GPs, geriatric nurse practitioner and secondary line geriatric nursing specialist will also keep track of the time spent on managing cases and coordinating tasks, time spent on conferring with health professionals, and time spent on multidisciplinary meetings per elder. A time tracking format will be developed to this end.

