**Figure 1 F1:**
[figure not shown]
The Walcheren Integrated Care Model (WICM).

The frail elderly aged 75+ years are identified by their general practitioner (GP) by the Groningen Frailty Indicator (GFI), a tool for the detection of frailty. The GFI is a 15-item questionnaire that measures decreases in physical, cognitive, social, and psychological functioning. Scores can range from 0 to 15 [39,40]. A geriatric nurse practitioner that works at the GP practice sends the GFI questionnaire to the homes of the elderly and then contacts them by telephone if they do not respond. When necessary, elderly are helped at home to complete the questionnaire. A geriatric nurse practitioner and GP calculate the GFI score. Elderly with a GFI ≥4 are identified as frail and assigned to a case manager. The geriatric nurse practitioner is the case manager for elderly with single needs. A secondary line geriatric nursing specialist is assigned as case manager if the needs are multiple or of a complex nature.

The case manager then sets up a meeting with the elderly to assess their needs with the EASYcare instrument. EASYcare is an evidence-based comprehensive need assessment instrument that assesses (instrumental) activities of daily life, cognition, and mood. It also contains a module for converting care requirements relating to welfare, residence, and care into treatment goals [41]. The goals are drawn up in consultation with the elderly and their caregivers. Explicit attention is paid to the necessary support and guidance of the caregivers. The results of the assessment are described by the case manager in an individualized care plan. The case manager also creates a proposal for required care and care objectives.

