The proposed plan is then discussed in a multidisciplinary meeting led by the GP. Depending on treatment goals, the meeting is also attended by other health professionals who may be needed. During the meeting, a multidisciplinary care plan will be approved, actions and care paths will be discussed, and agreements will be made about the care to be deployed and the activities of all persons involved. The treatment plans of each professional are included in the care plan. The GP harmonizes the care plan with the elderly and their caregiver and obtains permission for its implementation. A chain computerization system accessible by the health professionals involved will be used for the multidisciplinary care plan. The professionals will automatically receive an email in the event of changes in use of care or a transfer.

The case manager is responsible for admittance to the required services, the planning and coordination of care delivery, and periodical evaluation of the care plan. Thus, the case manager arranges obligatory need assessment, monitors the elderly at least every six months for one year, and supports the multidisciplinary team by arranging meetings and streamlining the necessary exchange of information. The responsibilities and activities of the involved professionals and case manager are formalized in agreed protocols with predefined modes of referral and collaboration. During the process, the GP practice functions as a single entry point. It is the gate through which elderly and professionals can access the expertise and services of all health and social care professionals and organizations. The GP and case manager work in close collaboration to ensure timely and correct care assessment and provision. To be able to fulfill their tasks, the GPs must have completed an executive training in geriatric care, a course in GP consults and EASYcare training. The case managers must have successfully attended the EASYcare training and a course in case management.

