### Data collection and instruments: health professionals

Data on the outcomes will be collected from GPs, nursing home doctors, geriatrists, geriatric nurse practitioners, secondary line geriatric nursing specialists, specialists in hospitals, home care employees, mental health professionals, and paramedical specialties with the following instruments (see Table 3):

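### Meeting time is registered only by GPs and the two case-manager nurse roles, so no described source captures the meeting time of the other professionals who attend

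*Protocol article*

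**What the plan says.** Table 3 of the protocol article gives three sources for the objective burden of health professionals: the elder's own report, a time tracking form completed by the professional, and GP files.

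- **Form.** Table 3 does not say which professionals keep it. The section on the time tracking form does: "The GPs, geriatric nurse practitioner and secondary line geriatric nursing specialist will also keep track of the time spent on managing cases". The same section adds "time spent on conferring with health professionals, and time spent on multidisciplinary meetings per elder". The format does not yet exist: "A time tracking format will be developed to this end".
- **Volume route.** Under File research and questionnaire, "the volume of care will be multiplied by a mean time determined by consensus with the health professionals". The volume comes from the questions on self-reported use, which cover seven domains of care, and from GP files, which cover the same domains.
- **Who attends.** The description of the intervention has the GP lead the multidisciplinary meeting and adds that, depending on treatment goals, "the meeting is also attended by other health professionals who may be needed". The two nurse roles on the form are the case managers: "The geriatric nurse practitioner is the case manager for elderly with single needs", and "A secondary line geriatric nursing specialist is assigned as case manager if the needs are multiple or of a complex nature".
- **Whose outcomes.** The lead-in to the health-professional outcomes names a wider group, including "specialists in hospitals, home care employees, mental health professionals, and paramedical specialties".
- **Second use.** The cost-effectiveness section draws on the form, with the patient files and the questionnaire, to establish who delivered which care to each elder.

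**The concern.** The people who attend the meetings are a wider set than the people who record them. A geriatrician, social worker or home care employee who sits in a multidisciplinary meeting spends working time on the elder, but does not keep the form. The elder's care-use questions and the GP file extraction concern care that the elder uses, and a meeting between professionals is not among their domains.

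This is a choice about data collection, so a later analysis plan cannot repair it: time that was never recorded cannot be analysed. At stake is the answer to one part of the research question, the effect of the model on health professionals, and part of the cost side of the economic evaluation. Multidisciplinary consultation and meetings are one of the ten elements of the model, so the missing time is likely to fall more on the experimental side. The model's burden and cost would then look lower than they are. The primary quality-of-life outcome is not affected.

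**Working it through.** The article states no figure for meeting time, so there is nothing to reproduce. The check traces each kind of professional time to its described source.

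| Kind of time | GP and the two nurse roles | Other professionals |
|---|---|---|
| Direct care to the elder | Volume × mean time | Volume × mean time |
| Case management, coordination, conferring | Form | No source described |
| Multidisciplinary meetings | Form | No source described |

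The right-hand column is empty only for coordination, conferring and meetings. For meetings, the article itself says that other professionals take part.

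**Unrecorded share of meeting person-time.** Let t be the attendees who keep the form, k the attendees who do not, and let each spend equal time. Recorded person-time is proportional to t and true person-time to k+t, so the missed share is k/(k+t).

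The article gives neither k nor t; both are assumptions here. t=2 is a GP and one case manager. t=3 adds the second nurse role, which is possible because the geriatric nurse practitioner works at the GP practice. k=0 is possible because others attend only where treatment goals call for them.

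| k | t=2 | t=3 |
|---|---|---|
| 0 | 0/2 = 0% | 0/3 = 0% |
| 1 | 1/3 = 33% | 1/4 = 25% |
| 2 | 2/4 = 50% | 2/5 = 40% |
| 3 | 3/5 = 60% | 3/6 = 50% |

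**From meeting time to total burden.** If meetings make up a fraction f of true total professional time, the share of the total that is missed through meetings is f × k/(k+t). The article gives no number or length of meetings and no total time, so f is unknown and this product cannot be evaluated.

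**Direction.** Meetings are built into the model; the control practices give traditional care. The understatement is therefore probably larger in the experimental group. This is an inference from the two descriptions of care and not a stated fact.

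**The case against.** The strongest reply is that the form has not been designed. The article fixes who fills it in, not which fields it holds. If it lists attendees, the others' time can be derived, and a condensed article may leave that detail to a fuller document. The cost section also expects the combined sources to show from whom care came. This stands in part: the article does not rule out recording attendees. But nothing in it says that attendance will be recorded, and the text that names the form-keepers leaves out people it elsewhere places in the meeting.

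Limiting registration to the coordinating roles is also a reasonable way to contain workload, which the Discussion treats as a real worry. That supports keeping the same form-keepers, and the remedy does so.

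Three stronger readings are tempting, and the documents do not support them.

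- **All burden of the other professionals is lost.** It is not; their direct care time is still counted through the volume route. Nor does the wide list of professions mean that every instrument covers every profession, because that list introduces all the health-professional outcomes together.
- **The outcome is biased by 33% to 60%.** Those figures concern meeting person-time under assumed attendance, and 0% is possible. The denominator of the outcome is much wider.
- **Only the experimental group is affected.** The article does not say that traditional care lacks such meetings. It describes region-wide agreements on elderly care and other care-chains under development, and control GPs also register time. Other professionals' time at a control-side meeting would be missed in the same way.

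**Conclusion.** The concern holds in a limited form. As the article is written, the meeting time of professionals other than GPs and the two case-manager roles has no described source, and their side of conferring and coordination has none either. This probably understates professional burden more in the experimental group, and the model's cost wherever the form is the cost input. The direction rests on meetings being a model element while controls give traditional care.

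The unrecorded share of meeting person-time depends on attendance that the article does not give: none with no other attendees, a quarter to three fifths with one to three, assuming two or three tracked attendees and equal time each. The effect on total objective burden or on cost per QALY cannot be computed from the article. The point deserves action because it is cheap to settle before the form is built and cannot be repaired afterwards.

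**What to change.** When the form is developed, have the form-keeper enter, for each elder discussed, the meeting minutes and the roles present. Use the same entry in both groups, so that any multi-professional meeting in a control practice is counted in the same way. Derive meeting time as minutes summed over the roles present, and cost it on the same basis.

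If this is not done, label the time-tracking component as GP and case-manager time only, and state the limit in both the burden and the cost results. That label is needed in any case for conferring and coordination, which the added fields do not cover.

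The cost is a few seconds of registration per elder discussed, by staff who already record the meeting, with no extra form-keepers. The burden and cost figures for the model may become less favourable.
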